### Aim and objectives

The aim of the study is to investigate the effects of voluntary PFM pre-contraction alone during activities involving an increase of the intra-abdominal pressure (the Knack) for the treatment of female SUI.

The objectives are to compare the effectiveness of the Knack alone versus PFMT alone and PFMT + the Knack for the following measures:
Objective cure of urine leakage after intervention, defined as leakage of < 2 g (on the 1-h pad test) immediately after the intervention and 6 months after randomisation (primary outcome measure) [17].Lower urinary tract symptoms and impact of UI on the participants’ quality of life immediately after the intervention and 6 months after randomisation. These secondary outcomes will be assessed by means of the 3-day bladder diary, which considers the number of episodes of urine leakage on efforts [18]; the 1-h pad test, which evaluates the severity of urine leakage [17]; the International Consultation on Incontinence Questionnaire – Short Form (ICIQ-SF), which investigates urinary symptoms [19]; and the Incontinence Quality of Life Questionnaire (I-QoL), which is a measure of quality of life [20].Self-perceived efficacy of exercises immediately after intervention and 6 months after randomisation. This parameter will be assessed by means of the Self-Efficacy Scale for Practising Pelvic Floor Exercises [21]; satisfaction and desire to perform some other treatment immediately after the intervention and 6 months after randomisation (participants will be rated “satisfied” when they do not manifest a wish to perform some other treatment and as “dissatisfied” when they do wish to perform some other treatment) [18].PFM strength function as measured by digital palpation (PERFECT scheme) [22, 23], Peritron manometer [24] and pelvic floor dynamometry immediately after the intervention and 6 months after randomisation.

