## Methods

### Trial design

The study will be conducted at one single centre. It will consist of a prospective, randomised and controlled clinical trial: an intervention comprising 3 months of supervised treatment and a further 3 months of unsupervised treatment for a total of 6 months of follow-up. Assessments will be performed before and after (1 to 2 weeks after the end of treatment) the intervention and 6 months after randomisation and will include structured interviews, application of questionnaires, bladder diary, pad test and physical and gynaecological examinations (Table 1).

**Table 1 Tab1:** Schedule of enrolment, interventions and assessments

			STUDY PERIOD				
	Enrolment	Allocation		Post-allocation intervention delivery and research follow-up			
**TIMEPOINT**	***-t***_***1***_	**0 m**	***1-2 w***	***1 m***	***2 m***	***3 m***	***6 m***

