### Interventions

The participants will perform PFM exercises for 14 weeks in individual outpatient sessions supervised by an experienced physical therapist with training in pelvic floor rehabilitation. On weeks 1 and 2, the PFM training programme will be presented and taught (two outpatient weekly sessions) as per the allocation group. From weeks 3 to 14, the participants will perform PFM strength training, power and hypertrophy. The exercise programme for the first month will begin with a single outpatient session; then, the participants will perform the exercises at home and will visit the outpatient clinic 15 days later to resolve possible doubts and train under the supervision of a physical therapist [26]. At the end of the first month of training, the participants will visit the outpatient clinic to enhance the training programme by aiming to achieve greater recruitment of the involved muscles and avoid muscle adaptation [25]. The training protocol will be divided into three stages to allow for gradual progression of treatment. This is to say, the exercises will be gradually enhanced in the terms of duration, number of repetitions and position. Each stage will last 4 weeks (Table 3).

**Table 3 Tab3:** Details of the monthly training programmes

	The Knack group	PFMT group	PFMT + the Knack group
**Weeks 1–2**	Presentation and explanation of the exercise programme	Presentation and explanation of the exercise programme	Presentation and explanation of the exercise programme
**Weeks 3–6 (1st month)**	3 exercises in supine position: 8 repetitions (1 series) of each exercise 3 times per day, 3 days per week for a total of 108 monthly series + orientation to perform the Knack during ADL and WA	8 MVC of PFM in supine position sustained for 6 s (type I muscle fibres) with a resting interval twice as long between contractions, followed by 3 fast contractions (type II muscle fibres) 3 times per day, 3 days per week, for a total of 36 monthly series	8 MVC of PFM in supine position sustained for 6 s (type I muscle fibres) with a resting interval twice as long between contractions, followed by 3 fast contractions (type II muscle fibres) 3 times per day, 3 days per week, for a total of 36 monthly series 3 exercises in supine position: 8 repetitions (1 series) of each exercise 3 times per day, 3 days per week for a total of 108 monthly series + orientation to perform the Knack during ADL and WA

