#### Primary outcome measure

The primary outcome measure will be the objective cure of UI as assessed by means of the 1-h pad test 6 months after randomisation. For the 1-h pad test, the women will be asked to wear pre-weighed pads and drink 500 ml of sodium-free liquid in < 15 min. After rest, they will be instructed to exercise for 30 min, including walking, climbing up and down five flights of stairs (10×), jumping (10×), coughing vigorously (10×), bending to pick up an object from the floor (10×) and washing hands for 1 min in running water. Before and after the test, the weight of the pad will be measured with a high-precision balance to determine the amount of leakage. For the 1-h pad test, an increase of 1 to 10 g represents mild incontinence and 11 to 50 g represents moderate incontinence. Women with urine leakage ≥ 2 g will be included because the study will be conducted in a tropical country [17]. The objective cure of urine loss after the intervention will be defined as leakage < 2 g. The pad test is considered a relevant tool for the assessment of UI treatment success and has been widely used in this type of study [30–32].

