### Sample size calculation

The literature on the Knack is scarce and assessed only in combination with PFMT [16, 26]. The aim of this study is to investigate the effects of the Knack alone for the treatment of SUI. Because of the lack of scientific evidence a local pilot study was previously conducted to calculate the sample size (unpublished). Forty-five patients agreeing to participate by signing an informed consent form (Additional file 1) will be recruited. This group will be randomly allocated by means of online randomisation software (http://randomization.com) to the following groups: the Knack, PFMT or PFMT + the Knack. The primary outcome measure [objective cure as established by means of the 1-h pad test (leakage ≤ 2 g)] will be used to compare the effects of SUI treatment amongst the groups. At the end of the pilot study (after the last randomised patient completes the intervention), the percentage of cured participants will be compared amongst the groups. Based on a pilot study, it is observed that the PFMT group has a higher objective cure rate compared to the knack group, however, without statistical significance at the level of 5% (*p* value = 0.592 obtained through Fisher’s exact test). Although the knack group has an objective cure rate lower than that of the PFMT group, this objective cure rate is approximately equal to 50%. The premises for the sample calculation are the hypotheses: *H*_0_: θ_1_ − θ_2_ ≤ δ and *H*_*a*_: θ_1_ − θ_2_ > δ, where, θ_1_: response rate of the Knack group; θ_2_: response rate of the PFMT group (gold standard); *δ*: Non-inferiority margin (clinically relevant difference between the response rates of groups the Knack and PFMT, and that for the calculation of non-inferiority, the value of *δ* must be negative; *r*: ratio between sample sizes *n*_2_/*n*_1_ (*r* = 1 ⇒ *n*_2_ = *n*_1_); *α*: significance level (*α* = 5%); 1 − *β*: test power (*β* = 20% ⇒ 1 − *β* = 80%) [37]. Formula:
$$ {\displaystyle \begin{array}{c}{n}_1=\frac{{\left({z}_{\alpha }+{z}_{\beta}\right)}^2\left[r{\theta}_1\left(1-{\theta}_1\right)+{\theta}_2\left(1-{\theta}_1\right)\right]}{{\left({\theta}_1-{\theta}_2-\delta \right)}^2}\\ {}{n}_2={rn}_1\end{array}} $$

Notice that, here, *r* = 1 for equal size *n*_1_ = *n*_2−_

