Thus, according to the result of the pilot sample, at the 5% significance level, there is no significant difference between the groups in relation to the objective cure rate in the treatment of mild and moderate SUI, assessed by the 1-h pad test. Considering the premises: θ_1_= 42.9% and θ_2_= 71,4% (obtained through the analysis of the pilot sample), *δ* = − 7,14% (10% variation in relation to the response rate of the PFMT group, obtained through literature data [38], *r* = 1 (groups of equal sample sizes), *α* = 5% and *β* = 20% ⇒ power (1 – *β*) = 80%, we obtained a total of 122 patients (61 patients per group). Thus, considering a significance level of 5%, a sample of 122 patients (61 patients per group) has 80% power to show the non-inferiority of the knack technique compared to PFMT in the treatment of mild and moderate SUI, with a non-inferiority margin of − 7.14%, which corresponds to a variation of 10% in relation to the response rate of the PFMT group (gold standard), supposedly equal to 71.4% and assuming that the rate of response of the test group is 42.9%. The sample size calculation was based on the primary objective of comparing the Knack technique (experimental group) with PFMT (control group). However, we have a third group that associates the techniques PFMT + the knack, so, 183 participants will be recruited. It is also necessary to consider possible losses in the sample during the 6-month follow-up period, thus, we assume losses of 0 to 15% based on previously published studies [39, 40]. Thus, we will recruit nine more participants per group, increasing the total number of participants to 210.

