**Fig. 1 Fig1:**
[figure not shown]
CONSORT flowchart

Descriptive statistics will be performed for sample characterisation. Categorical variables will be expressed as the distribution of frequencies, and numerical variables by means of measures of central tendency and variability. The mean, standard deviation, 95% confidence interval, median and maximum and minimum values will be calculated for the analysis of the primary outcome measure (pad test). The primary outcome measure (pad test) will be compared within and amongst groups (the Knack, PFMT and the Knack + PFMT) (before and after intervention) using an ANOVA. All statistical analyses will be performed using the current version of SPSS software after the last patient undergoes the final assessment after intervention. The same approaches and statistical procedures used for the primary outcome measures will be employed for the analysis of the secondary outcome measures.

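### The primary time point is inconsistent: the objectives make cure primary at end of intervention and at 6 months, while the outcome section makes it primary at 6 months only

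*Protocol article*

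**What the plan says.** All references are to the protocol article.

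- **Aim and objectives.** The first objective is cure below 2 g on the 1-h pad test, "immediately after the intervention and 6 months after randomisation (primary outcome measure". The primary label follows two times, with no rule on whether success is needed at either or at both.
- **Primary outcome measure.** Only one time is named here: "The primary outcome measure will be the objective cure of UI as assessed by means of the 1-h pad test 6 months after randomisation". Later in the same section, cure is defined simply as leakage under 2 g following the intervention.
- **Statistical analysis.** The pad test is compared within and among the three groups, "before and after intervention) using an ANOVA". Six months is not named. The Methods paragraph of the Abstract uses the same phrase.
- **Trial design.** Visits take place "before and after (1 to 2 weeks after the end of treatment) the intervention and 6 months after randomisation", so the end-of-treatment and 6-month visits are separate. The preceding sentence, however, describes the intervention as 3 supervised months plus 3 unsupervised months.
- **Table 1.** After baseline, the pad test is scheduled at 3 months and at 6 months.
- **Sample size calculation.** There is one significance level and one pair of cure rates: "considering a significance level of 5%, a sample of 122 patients (61 patients per group) has 80% power". The pilot cure rates were to be compared "after the last randomised patient completes the intervention"; 6 months is not mentioned there.

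**The concern.** The result at the end of supervised treatment and the result after a further 3 unsupervised months answer different questions. The second also depends on whether women keep exercising once supervision stops, so the two can disagree. Table 1 ensures that both will be available.

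With two statements of the primary time point and nothing to rank them, a report could present either time as primary and cite the protocol for it. The single 5% level in the sample size makes no allowance for that choice. If both times were meant to be required, the sample size makes no allowance for that either.

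**Working it through.** **1. Do the statements agree?**

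| Section | Primary time point |
|---|---|
| Aim and objectives | End of intervention and 6 months |
| Primary outcome measure | 6 months |
| Statistical analysis; Abstract (Methods) | Before and after intervention; 6 months not named |

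The first two rows conflict. The parenthesis in the objectives could grammatically attach to 6 months alone. But the same two-time phrase recurs for the secondary outcomes, where it plainly means both visits, so the natural reading is both.

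**2. Does the analysis wording decide it?** It depends on what intervention means, and Trial design uses the word in two ways.

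- Narrow sense: the post-intervention visit falls 1 to 2 weeks after treatment ends. The Interventions section states "The participants will perform PFM exercises for 14 weeks in individual outpatient sessions", so this visit is at about week 14 + 1 = 15 to 14 + 2 = 16, against about week 26 for 6 months. The analysis would then point to the end of treatment.
- Broad sense: the intervention includes the 3 unsupervised months, so the 6-month visit is itself post-intervention. The Primary outcome measure section also describes cure as following the intervention, straight after fixing 6 months.

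Both senses are in the text, so the phrase is ambiguous.

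**3. How many tests does the sample size assume?** Inputs from Sample size calculation: Knack cure rate θ₁ = 0.429, PFMT cure rate θ₂ = 0.714, margin δ = −0.0714, α = 5%, power 80%, equal groups. With the standard variance term,

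n = (z_α + z_β)² [θ₁(1−θ₁) + θ₂(1−θ₂)] / (θ₁ − θ₂ − δ)²

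= 6.1826 × (0.2450 + 0.2042) / (−0.2136)² = 6.1826 × 0.4492 / 0.04562 = 60.9, so 61 per group.

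This reproduces the stated 61 as one test at one-sided 5%. (The formula as printed, with θ₂(1−θ₁), gives 88.4, so 89.) At one-sided 2.5% the same formula gives 77.3, so 78. The stated figure therefore contains no adjustment for two times.

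**4. If success at either time counted.** Take two one-sided 5% tests with bivariate normal statistics of correlation ρ. The document gives no ρ, so the values are assumed.

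Error = 1 − P(Z₁ < 1.645, Z₂ < 1.645)

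| ρ | Type I error |
|---|---|
| 0 | 1 − 0.95² = 9.75% |
| 0.5 | 8.8% |
| 0.7 | 8.0% |
| 0.8 | 7.5% |
| 0.9 | 6.8% |

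A Bonferroni split to 2.5% each would move the plan's own formula from 61 to 78 per group.

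**5. If both times were required.** The type I error is not inflated. With a nominal 80% power at each time, joint power = P(Z₁ < 0.8416, Z₂ < 0.8416), which is 0.80² = 64% at ρ = 0, 69% at ρ = 0.5 and 73% at ρ = 0.8. The 80% is taken as the plan's nominal figure; whether the assumed rates support it is a separate question.

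**The case against.** The strongest reply is that the section headed Primary outcome measure gives one time point, 6 months, and that a dedicated definition normally outranks a list of objectives. That is a good reason to adopt 6 months in the repair. It does not remove the conflict: the article states no order of precedence, and the analysis text does not carry the 6-month definition through.

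A second reply concerns the analysis wording. A reader might infer that the before-and-after phrase is a third version of the primary time point, and that read literally it drops the 6-month visit. The document does not support that. Trial design also describes the intervention as covering all 6 months, and the outcome section uses the same loose expression right after naming 6 months. Statistical analysis adds that analyses wait until the last patient's final post-intervention assessment; since the last pad test in Table 1 is at 6 months, this fits the 6-month visit at least as well. The phrase leaves the matter open and contradicts neither statement.

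A third reply is that the error rates need a rule the plan does not state. This stands. The objectives join the two times with the word and, and no either-time rule appears anywhere. The figures show what each way of resolving the ambiguity would cost; they are not the error rate of the plan as written.

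That a separate analysis plan may exist does not answer the point. The article states the primary time point in two ways that differ, which is not the same as leaving detail out.

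**Conclusion.** The concern holds as an inconsistency between Aim and objectives (two primary times) and Primary outcome measure (6 months only), which the Abstract and Statistical analysis leave unresolved.

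Its size depends on how the ambiguity would be used. Allowing success at either time would raise a one-sided 5% error to about 7.5% to 8.8%, with a ceiling of 9.75% under independence. Requiring both would lower a nominal 80% power to about 69% to 73%. Both ranges rest on an assumed correlation of 0.5 to 0.8 and on the bivariate normal approximation. With a single primary time point neither applies, and the stated 61 per group needs no change for multiplicity.

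The point matters because it determines which result the trial rests on, and both candidate results will be collected.

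**What to change.** 1. **Primary outcome measure:** keep cure (leakage under 2 g) at 6 months after randomisation as the single primary time point.
2. **Aim and objectives:** attach the primary label to 6 months alone and call cure immediately after the intervention secondary.
3. **Statistical analysis and Abstract (Methods):** state that the primary between-group comparison is at 6 months after randomisation. Keep the end-of-intervention comparison and the within-group comparisons with baseline as secondary. Simply replacing the before-and-after phrase would delete the planned comparison with baseline, so the sentence needs adding to as well as correcting.
4. **Sample size calculation:** state the time to which the pilot cure rates refer, since 6 months is not named there.

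The cost is wording in three or four places. No visit, measurement or multiplicity adjustment changes. Trial status reports 185 of 210 participants recruited, so the change should be made and dated before any analysis by arm, and recorded in the trial registry, as that section already provides for protocol changes.

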## Methods

### Trial design

The study will be conducted at one single centre. It will consist of a prospective, randomised and controlled clinical trial: an intervention comprising 3 months of supervised treatment and a further 3 months of unsupervised treatment for a total of 6 months of follow-up. Assessments will be performed before and after (1 to 2 weeks after the end of treatment) the intervention and 6 months after randomisation and will include structured interviews, application of questionnaires, bladder diary, pad test and physical and gynaecological examinations (Table 1).

**Table 1 Tab1:** Schedule of enrolment, interventions and assessments

			STUDY PERIOD				
	Enrolment	Allocation		Post-allocation intervention delivery and research follow-up			
**TIMEPOINT**	***-t***_***1***_	**0 m**	***1-2 w***	***1 m***	***2 m***	***3 m***	***6 m***
**ENROLMENT:**							
**Eligibility screening**	X						
**Informed consent**		X					
**Allocation**		X					
**INTERVENTIONS:**							
***The knack group***			X	X	X	X	
***PFMT group***			X	X	X	X	
***The Knack + PFMT group***			X	X	X	X	
**ASSESSMENTS:**							
***Basic socio-demographic data***		X					
***BMI***		X					
***General health status Medical history and medication***		X					
***Parity and obstetric history***		X					
***Type and duration of SUI***		X					
***3-day bladder diary***		X				X	X
***1-h pad test***		X				X	X
***ICIQ-SF***		X				X	X
***PERFECT scheme***		X				X	X
***Dynamometry***		X				X	X
***Vaginal squeeze pressure***		X				X	X
***I-QoL***		X				X	X
***Frequency of the outpatient sessions***			X	X	X	X	
***Adherence to the home exercises***				X	X	X	X
***Self-efficacy and expectation***		X				X	X
***Subjective cure of SUI***						X	X
***Adverse events***			X	X	X	X	X

*PFMT* pelvic floor muscle training, *ICIQ-SF* International Consultation on Incontinence Questionnaire – Short Form, *I-QoL* Incontinence Quality of Life Questionnaire, *BMI* body mass index, *SUI* stress urinary incontinence, *m* month, *w* week

### Research site

The study will be conducted at the Urogynaecology and Vaginal Surgery outpatient clinic, Department of Gynaecology, Universidade Federal de São Paulo (UNIFESP), Brazil.

### Participants

The study population will comprise women with mild to moderate SUI or mixed urinary (MUI). The diagnosis of SUI will be based on the patient’s report of leakage during physical stress and report of the condition that bothered them the most in case of mixed urinary incontinence (stress urinary or urgency incontinence) and confirmed by means of the 1-h pad test (leakage ≥ 2 g) [17]. Leakage up to 10 g will be rated as mild SUI and 11 to 50 g leakage as moderate SUI [17]. The sample will also include women with grade 2 muscle strength (normal contraction with an elevation of the anterior vaginal wall) on the two-finger assessment rated according to the Oxford scale [22, 23].

### Recruitment

Participants will be recruited from the Urogynaecology and Vaginal Surgery outpatient clinic, Department of Gynaecology, UNIFESP. The eligibility criteria will be applied in two steps: (1) women with urinary symptoms will be assessed by a urogynaecologist, who will perform a clinical examination (clinical and physical examinations, including the cough stress test) [1] and the 1-h pad test [17]; next, the patients will be referred to the physical therapy unit, where conservative treatment will be offered; (2) a physical therapist specialised in pelvic floor rehabilitation will provide instruction on the location and function of the PFM by means of oral explanations and anatomical illustrations; teach the patients how to correctly contract the PFM checked by means of two-finger palpation (four sessions to learn how to correctly perform contractions) [25]; and invite the patients who learned how to correctly perform PFM contractions and with grade 2 muscle strength [22, 23] to participate in the study. Patients who agree to participate will be requested to sign an informed consent form (Additional file 1).

The eligibility criteria are described in Table 2. Patients who do not meet the inclusion criteria will be referred back to the physician to receive treatment for UI. Eligible patients who complete the assessment will be randomly allocated into the study groups: (1) the Knack, (2) PFMT and (3) the Knack + PFMT.

**Table 2 Tab2:** Inclusion and exclusion criteria

